## Outcome assessment

### Primary outcome: recruitment

The primary outcome of this trial is recruitment. Data logs will be kept to assess:the number of patients screened for eligibility,the proportion of eligible patients consenting to participation and reasons for non-participation,the proportion of consenting patients undergoing randomisation and reasons for non-randomisation,the proportion of patients not receiving their randomised allocation and the reasons for this.The combination of quantitative and qualitative data regarding recruitment will enable us to understand the potential pool of eligible patients and reasons for non-participation and withdrawal throughout the recruitment process. This will enable us to further refine and develop our recruitment and randomisation processes for a definitive, phase III trial.

### Secondary outcomes

#### Safety

To assess the safety profile of acute laparoscopic surgery, the following outcomes will be assessed: conversion rates from laparoscopic surgery to open surgery, intraoperative and postoperative complication rates, the severity of postoperative complications using the Clavien-Dindo grading system, the incidence of patient-safety indicators and 30-day postoperative mortality rates.

#### Endpoint evaluation to identify the optimal primary endpoint(s) for a definitive phase III trial

A range of key outcomes will be collected, including:Clinical outcomes including length of high dependency unit/intensive care unit stay, length of hospital stay, resumption of gastrointestinal function and oral intake, opioid analgesic use, reoperation rates and readmission rates and details regarding histopathology of the resected specimen;Patient-reported health-related quality-of-life data using the Gastrointestinal Quality of Life Index, the Short Form - 12 Health Survey, pain scores using the Brief Pain Inventory and the EuroQol-5D-5L;Resource use using dedicated patient-reported and site-completed Health Economics Questionnaires to measure primary and secondary healthcare service use;Patient and clinician acceptability of trial processes and procedures using in-depth qualitative interviews and a dedicated Patient Feedback Questionnaire.

These candidate endpoints will be explored quantitatively and qualitatively to assess for completion rates, generate data to inform future power calculations and to identify which endpoint will be of most meaning and value to clinicians and patients as a primary endpoint for a definitive phase III trial. Candidate endpoints will be collected at various times during the course of the trial (table 1). Trial follow-up will cease when the last participant reaches 6 months postrandomisation.

**Table 1 T1:** Schedule of events

	Pretrial diagnostics	Baseline	Operative	3-Day postoperative review	7-Day postoperative review	30-Day postoperative review	3, 6 and 12* months postoperative assessment
Radiological/endoscopic diagnosis	✓						
Medical assessment		✓		✓	✓	✓	✓
Participant completed questionnaires		✓		✓	✓	✓	✓
Operative details			✓				
Complications			✓			✓	✓
Patient-safety indicators					✓ At discharge		✓†
Patient Feedback Questionnaire					✓		
Blinding Questionnaire					✓		
Resource usage			✓		✓ At discharge		

*Trial follow-up will cease when the last participant reaches 6 months postrandomisation.

†In-patients only

## Qualitative substudy

Trial processes and their acceptability to clinicians and patients will be assessed using semistructured, in-depth qualitative interviews to optimise and design strategies for a definitive, phase III trial. Clinicians will be interviewed regarding overall trial processes, recruitment in the emergency setting and potential primary endpoints for a future phase III trial. Patients will be interviewed to identify any issues with the randomisation process, preferential bias for one type of surgery, reasons for non-participation or withdrawal, refusal of treatment allocation and burden of participation.

## Sample size calculation and statistical analysis

The sample size has been chosen to allow the estimation of the parameters of interest to the necessary degree of precision, following the recommended rule-of-thumb of 30 participants per arm.^17^ The sample size has been calculated to account for a 10% attrition rate and aims to recruit at least 66 patients. This sample size will allow the estimation of morbidity and mortality rates with the laparoscopic arm with 95% two-sided CIs of at most ±17%, allowing its safety profile to be demonstrated. Achievement of this recruitment target will also demonstrate feasibility of a likely required recruitment rate for a successful, definitive, phase III trial.

The feasibility of recruitment and randomisation will be evaluated by summarising the screening, eligibility, consent and randomisation processes, including numbers of participants involved during each stage. Descriptive summaries of the participant recruitment pathways at the five recruiting centres will be presented. Reasons for non-participation in the study will be summarised. Participant retention during follow-up, including number of participants completing/withdrawing from the study and reasons for withdrawal, will be presented by treatment arm. Completion rates of data collected at the baseline and follow-up visits will be summarised. The Bang Blinding Index at 7 days and the timings of non-blindings will be reported to inform the feasibility of blinding in a phase III trial. In addition, the relationship between patients, surgical team members and centres will be described to indicate the clustering structure of the feasibility study to inform the design of a phase III trial. The safety profile of each treatment arm will be summarised through descriptive statistics. Mortality rates, intraoperative and postoperative complication rates, conversion rates and patient-safety indicator rates will be reported with 95% CIs. All analyses will be conducted on an intention-to-treat basis. An analysis formally comparing the two treatment arms will not be performed due to the lack of power within this feasibility study, in addition to the purpose of this study.

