**Methods and analysis:**

The LaCeS feasibility trial is a prospective, multicentre, single-blinded, parallel group, pragmatic randomised controlled feasibility trial. Patients will be randomised on a 1:1 basis to receive either

laparoscopic or open surgery. The trial aims to recruit at least 66 patients from five acute general surgical units across the UK. Patients over the age of 18 with a diagnosis of acute colorectal pathology requiring resection on clinical and radiological/endoscopic investigations, with a National Confidential Enquiry into Patient Outcome and Death classification of urgent will be considered eligible for participation. The primary outcome is recruitment. Secondary outcomes include assessing the safety profile of laparoscopic surgery using intraoperative and postoperative complication rates, conversion rates and patient-safety indicators as surrogate markers. Clinical and patient-reported outcomes will also be reported. The trial will contain an embedded qualitative study to assess clinician and patient acceptability of trial processes.

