## Background

Emergency general surgery is a huge clinical service, with approximately 1000 finished consultant episodes per 100 000 population/year.^1 2^ Approximately 30% of emergency admissions are secondary to colorectal pathology, namely, colorectal malignancy, inflammatory bowel disease and diverticular disease.^3 4^ More than 30 000 patients undergo an emergency laparotomy for a variety of intra-abdominal pathologies each year within the National Health Service (NHS) in England and Wales.^5^ In the UK, the National Emergency Laparotomy Audit (NELA) reported outcomes on 23 198 patients, of which 37% underwent an emergency colorectal resection between December 2014 and November 2015.^6^ The burden of emergency surgery is significant, with reports of 30-day postoperative morbidity rates of 33%–71% and mortality rates of 14%–17%.

The NELA audit reports that the majority of emergency surgery is undertaken using an open approach, with approximately 14% of all emergency abdominal operations commenced laparoscopically, of which only half are completed laparoscopically.^6^ The role of laparoscopic surgery in certain acute intra-abdominal pathologies (ie, acute appendicitis) has been well elucidated in a number of randomised controlled trials, with reports of improved pain, shorter recovery and reduced length of hospital stay.^7 8^ Consequently, laparoscopic appendicectomy has become a well-established technique.^9^ In comparison, the current evidence of acute laparoscopic colorectal resection consists of a number of case series and cohort studies, which are limited by their retrospective nature, strict patient selection and small sample size.^10 11^ The evidence base for laparoscopic surgery in the elective colorectal surgery is vast.^12 13^ However, applying this evidence to the acute setting is inappropriate due to the varying levels of sepsis, differing patient physiology and potentially more advanced disease states. The only way to integrate laparoscopic surgery in the algorithm for acute colorectal pathology is to evaluate its safety and efficacy within the remit of a randomised controlled trial.

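### The worst-case precision of ±17% for the laparoscopic arm assumes all 33 patients contribute; at the plan's own 30 per arm after attrition it is about ±18% (minor)

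*Protocol article*

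**What the plan says.** The section on sample size and statistical analysis makes three linked statements. The size is chosen "following the recommended rule-of-thumb of 30 participants per arm". It then allows for loss: "The sample size has been calculated to account for a 10% attrition rate and aims to recruit at least 66 patients". Next it claims that this size will estimate "morbidity and mortality rates with the laparoscopic arm with 95% two-sided CIs of at most ±17" percentage points, and presents this as sufficient to demonstrate the safety profile of laparoscopic surgery.

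The abstract gives the allocation: "Patients will be randomised on a 1:1 basis to receive either" laparoscopic or open surgery. That is 33 per arm at the minimum target. The Background cites "30-day postoperative morbidity rates of 33%–71% and mortality rates of 14%–17" per cent for emergency surgery.

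The article does not say which number of patients or which assumed rate lies behind the 17%, nor when during follow-up the 10% is expected to be lost.

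**The concern.** The plan adds patients to cover attrition and then appears to quote the precision that would apply if nobody were lost. The claim is worded as an upper bound, so it has to hold in the least favourable case the plan allows for: a rate near 50% with the planned number of evaluable patients.

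This is the article's only numerical precision claim for the safety objective. The plan will report mortality, complication, conversion and patient-safety-indicator rates with 95% confidence intervals. A reader who compares those intervals with the promised bound could find a mid-range morbidity interval wider than the protocol said it could be. Recruitment, the conduct of the trial and any decision rule are not at stake.

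**Working it through.** **Inputs.** Total of 66, target of 30 per arm, 10% attrition, and 95% two-sided intervals, all from the sample size section. Allocation 1:1, hence 66/2 = 33 per arm. The assumed rate is not stated; an upper bound implies p = 0.5, and 50% lies inside the cited morbidity range. The formula is the normal-approximation half-width, 1.96 × √(p(1−p)/n).

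**1. Reproduce the plan's figure.** With n = 33 and p = 0.5: 1.96 × √(0.25/33) = 0.1706, or 17.06%. This rounds to the stated 17%. The unrounded n for exactly 17% is 0.25 × (1.96/0.17)² = 33.2, so 33 meets the bound to the precision stated.

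**2. Repeat at the plan's evaluable number.** With n = 30: 1.96 × √(0.25/30) = 0.1789, or 17.9%. Taking 10% off 33 literally gives 33 × 0.9 = 29.7, and the half-width is 18.0%.

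**3. Find the rates affected.** At n = 30 the half-width exceeds 17% when p(1−p) > 30 × (0.17/1.96)² = 0.2257. That is p between 0.5 − √(0.25 − 0.2257) and 0.5 + √(0.25 − 0.2257), about 0.34 to 0.66.

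**4. Evaluate at the rates cited in the Background, with 50% added.**

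| Rate | n = 33 | n = 30 |
|---|---|---|
| 14% (mortality, low) | ±11.8% | ±12.4% |
| 17% (mortality, high) | ±12.8% | ±13.4% |
| 33% (morbidity, low) | ±16.0% | ±16.8% |
| 50% (worst case) | ±17.1% | ±17.9% |
| 71% (morbidity, high) | ±15.5% | ±16.2% |

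Only mid-range morbidity breaches the bound.

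**5. Check other interval methods at n = 30.** Half the total length of a Wilson or Agresti-Coull interval at 50% is 16.85%. The Wilson interval is generally not centred on the estimate, and its longest side over all possible counts is 17.9%. That occurs at 10/30, where the interval is 19.2% to 51.2%. For Clopper-Pearson, the maximum half-length is 18.7% and the longest side 19.5%.

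**6. Check the attrition arithmetic.** 60 × 1.10 = 66, whereas 60/0.9 = 66.7. With 10% loss, 66 leaves 66 × 0.9 = 59.4, or 29.7 per arm, which is 0.3 of a patient below 30. Put the other way, 66 recruits keep 60 if loss is no more than 1 − 60/66 = 9.1%.

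**The case against.** **The bound is attached to the 66 recruited, and early safety data may be nearly complete.** Analysis is by intention to treat. Conversion, intraoperative complications and 30-day mortality are recorded early, so the 10% loss may fall mainly on later follow-up. This has force: if all 33 contribute, ±17% is right to rounding. A reader might infer that the attrition allowance and the precision claim contradict each other outright. The documents do not support that, because they do not say that the 10% applies to the safety rates. Nor do they say that it does not. The attrition sentence comes immediately before the precision claim, and the schedule of events also collects complications at 3, 6 and 12 months. The objection shows that the claim can hold, not that it holds under the plan's stated allowance.

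**No interval method is named, and Wilson gives 16.85% at 30.** So it would be too strong to say that 17% is attainable only with 33 patients. But Wilson meets it only as half the total length. Read as a distance from the estimate, which is the natural sense of ±, its longer side is again 17.9%. Naming the method can reasonably be left to the analysis plan, and its absence here is not a fault.

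**The attrition arithmetic.** A reader might infer that 66 is the wrong sample size. A shortfall of 0.3 of a patient per arm against a rule of thumb, with a target worded as a minimum, is rounding.

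**The importance of the claim.** The size also rests on the 30-per-arm rule and on showing a feasible recruitment rate, and recruitment is the primary outcome. The ±17% is a secondary descriptor, and this part of the objection stands in full.

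**Conclusion.** The point holds as a minor error of statement. The quoted worst-case precision belongs to 33 laparoscopic-arm patients with no loss. At the 30 per arm that the plan designs for, the bound is 17.9%, about one percentage point wider. The excess is confined to rates of roughly 34% to 66%, which the cited morbidity range includes; precision for mortality at the cited rates is not affected.

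This rests on three assumptions: the normal approximation, a worst-case rate of 50%, and attrition that reduces the denominator for the safety rates. The plan states none of them, though the first two reproduce its own 17% at n = 33. The finding does not support a larger sample or any doubt about the trial's feasibility aims. No formal comparison of arms is planned, and no threshold in the article depends on the figure.

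**What to change.** Replace the precision sentence with one that gives the number of patients and the assumed rate. For example: *the 95% two-sided confidence interval for a rate in the laparoscopic arm will have a half-width of at most about ±17% if all 33 patients contribute, or about ±18% with 30 evaluable after 10% attrition (normal approximation, rate 50%)*. If the sponsor expects the early safety outcomes to be complete for everyone randomised, a clause saying so would justify keeping ±17% for those outcomes.

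The cost is one sentence, with the stated worst-case precision about one point less favourable. The target of 66 and the attrition allowance can stay as they are, and no extra patients are needed.

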## Recruitment and randomisation process

All patients with suspected acute colorectal pathology will be assessed clinically, radiologically and/or endoscopically as per best clinical practice. Following confirmation of clinical and radiological/endoscopic diagnosis of an acute colorectal pathology requiring resection, patients will be approached for participation in the trial. Patients will only be approached for potential participation between the hours of 08:00 – 22:00.

Patients who are deemed to have temporary impairment in their judgement (temporary lack of mental capacity), related to their condition (eg, experiencing significant pain/distress/nausea or acute delirium secondary to sepsis), can be entered into the trial if a personal consultee can be identified to advise about trial entry. A personal consultee will ideally be a family member or partner, and will be informed of all key trial processes. Once the patient regains capacity, written informed consent will be requested from the patient for ongoing participation within the trial. Given the emergency nature of the trial, the time available to consider participation will be shorter than in the elective setting. Patients and personal consultees will be given as long as they need to consider participation in the trial. Ideally, this will be at least 2 hours.

Following appropriate surgical and anaesthetic assessment and confirmation of the clinical diagnosis, patients will be randomised using a telephone or online randomisation system, on a 1:1 basis to receive either laparoscopic or open surgery. Patients will be stratified to one of the two arms according to intended consultant surgeon in charge, age, body mass index, American Society of Anesthesiologists status, nature of underlying pathology and intended surgical procedure.

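### The sample-size section says laparoscopic safety can be demonstrated, but with no safety criterion, no comparison and 30 to 33 patients it can only be described

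*Protocol article*

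**What the plan says.** The point sits in the Protocol article, section Sample size calculation and statistical analysis. The trial is sized "following the recommended rule-of-thumb of 30 participants per arm". The section adds: "The sample size has been calculated to account for a 10% attrition rate and aims to recruit at least 66 patients". Allocation is "on a 1:1 basis to receive either laparoscopic or open surgery" (Recruitment and randomisation process), so 33 are randomised to each arm.

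The section then makes its precision statement: "This sample size will allow the estimation of morbidity and mortality rates with the laparoscopic arm", with "95% two-sided CIs of at most ±17"%, and gives the purpose of that precision as "allowing its safety profile to be demonstrated".

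The next paragraph describes the safety analysis. Each arm is to be summarised descriptively, and "Mortality rates, intraoperative and postoperative complication rates, conversion rates and patient-safety indicator rates will be reported with 95% CIs". It also says that the arms will not be formally compared, citing lack of power and the purpose of the study.

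The only mortality and morbidity figures in the article are in the Background, for emergency surgery as a whole: "30-day postoperative morbidity rates of 33%–71% and mortality rates of 14%–17"%. The Secondary outcomes sections speak of assessing safety, not of demonstrating it. No acceptable rate, margin or threshold for safety appears anywhere in the article.

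**The concern.** To demonstrate safety, a trial needs something to demonstrate it against: an acceptable rate, a margin, or a control arm with a planned comparison. This article states none of the first two and rules out the third. An interval half-width by itself does not separate an acceptable result from an unacceptable one.

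The sample-size sentence therefore credits the design with a property that the analysis paragraph of the same section does not deliver. The limitations list does not correct this, because it admits lack of power for efficacy only.

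What is at stake is how the safety results are read when a phase III trial is planned. Five deaths among 33 laparoscopic patients is 15%, inside the cited 14% to 17%. The wording invites a reader to treat that as safety shown, although the exact interval reaches about 32%.

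**Working it through.** **Inputs.** 95% two-sided confidence, a rule of thumb of 30 per arm, 10% attrition, a total of at least 66 and 1:1 allocation (sample-size and randomisation sections); mortality 14% to 17% (Background). Doubled, that mortality is 28% to 34%.

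**1. Numbers per arm.** 60 × 1.1 = 66, so 33 per arm; 33 × 0.9 = 29.7, about 30 after attrition. Both sizes are carried below, since attrition may or may not affect mortality data.

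**2. The plan's ±17%.** The Wald half-width is 1.96 × √(p(1−p)/n), largest at p = 0.5.
- n = 33: 1.96 × √(0.25/33) = 17.1 points. This reproduces the stated figure.
- n = 30: 1.96 × √(0.25/30) = 17.9 points. At 15 of 30 the exact (Clopper-Pearson) half-width is 18.7 and the Wilson half-width 16.8.

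So ±17% is a worst case at the number randomised. At the number left after attrition it is slightly exceeded by the Wald and exact methods, but not by Wilson.

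**3. Intervals near the cited mortality.**

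| Deaths | Rate | Exact 95% CI | Wilson upper | Wald upper |
|---|---|---|---|---|
| 3/30 | 10.0% | 2.1% to 26.5% | 25.6% | 20.7% |
| 4/30 | 13.3% | 3.8% to 30.7% | 29.7% | 25.5% |
| 5/30 | 16.7% | 5.6% to 34.7% | 33.6% | 30.0% |
| 5/33 | 15.2% | 5.1% to 31.9% | 30.9% | 27.4% |
| 6/33 | 18.2% | 7.0% to 35.5% | 34.4% | 31.3% |

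Whether a doubling is excluded depends on the count, on the method, and on whether the benchmark is 28% or 34%.

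**4. How often a doubling would be excluded.** For a true rate p0, find the largest death count x* whose upper limit lies below 2 × p0. The probability is then P(X ≤ x*) with X ~ Binomial(n, p0).

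| n | p0 | 2 × p0 | Exact: x*, probability | Wilson: x*, probability | Wald: x*, probability |
|---|---|---|---|---|---|
| 30 | 14% | 28% | 3, 37.9% | 3, 37.9% | 4, 58.7% |
| 30 | 17% | 34% | 4, 40.5% | 5, 59.7% | 5, 59.7% |
| 33 | 14% | 28% | 3, 30.3% | 4, 50.1% | 5, 68.8% |
| 33 | 17% | 34% | 5, 50.1% | 5, 50.1% | 6, 67.5% |

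The range is about 30% to 50% with exact intervals and at most about 69% with any of the three methods. An 80% chance with exact intervals would need about 75 patients in the arm at 14%, or about 61 at 17%.

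**5. The reverse view.** With 33 patients, P(X ≤ 5) is 13.2% if true mortality is 25% and 32.9% if it is 20%. A count that looks like the cited rate is therefore not rare when the true rate is clearly higher.

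**6. Morbidity.** 15 of 30 (50%) has an exact interval of 31.3% to 68.7%. That covers nearly all of the 33% to 71% range cited in the Background.

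**The case against.** The strongest reply is that the disputed verb is only loose. A safety profile can be shown without claiming that the operation is safe, and everything else in the article is descriptive: rates with intervals, no comparison, objectives worded as assessment, recruitment as the primary outcome. No rule turns a mortality figure into a verdict of safety. That stands as far as it goes, and it means the planned analysis itself needs no change. It does not rescue the sentence. If description is meant, the sentence should say so; if demonstration is meant, the design cannot deliver it.

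Four stronger readings are tempting, and the documents do not support them.
- A reader might infer that intervals on about 30 patients can never exclude a doubling of mortality. They can: three or fewer deaths in 30 exclude 28% by all three methods, and 5 of 33 excludes 34% even with the exact interval.
- A reader might infer that ±17% says nothing about mortality. It is stated as an upper bound. At 5 of 33 the exact interval runs 15.2 − 5.1 = 10.1 points below the estimate and 31.9 − 15.2 = 16.7 above, both within 17.
- A reader might infer that the trial is committed to declaring laparoscopic surgery safe. The wording invites that conclusion, but nothing in the plan requires it.
- A reader might infer from the ± form that Wald intervals will be reported, which collapse to 0% to 0% with no events. The article names no interval method, and that choice can properly sit in an analysis plan that is not shown.

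The benchmark is also open to challenge. The 14% to 17% is for emergency surgery in general, while this trial excludes patients needing inotropic support and requires suitability for both approaches. Its mortality may differ.

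**Conclusion.** The point holds in a limited form. The claim that safety can be demonstrated has no support in the stated design, because there is no criterion and no comparison; this does not depend on any interval method or benchmark. The size of the gap does depend on assumptions: true mortality equal to the cited 14% to 17%, and 30 to 33 patients analysed. Under those, a doubling would be excluded about 30% to 50% of the time with exact intervals and at most about 69% with Wald, so the intervals cannot be relied on for it.

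The ±17% itself is reproducible and is not an error; it simply belongs to 33 patients, not 30. The sample size, data collection and planned summaries are unaffected. The sentence should be corrected because it overstates what the trial can conclude about safety.

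**What to change.** In the sample-size section, replace the clause "allowing its safety profile to be demonstrated" with wording to this effect: *so that safety in this arm can be described with limited precision; no conclusion of safety or non-inferiority will be drawn*.

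Beside it, state what the intervals are expected to look like: about 5% to 32% at about 15% mortality (exact, 5 of 33) and about 31% to 69% at 50% morbidity (exact, 15 of 30). If ±17% is kept, say that it is the worst case at 33 patients and give the value at 30 after attrition (17.9 points by Wald, 18.7 exact).

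The cost is wording only. The downside for the sponsor is that the stated safety claim becomes more modest.

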## Secondary outcomes

Key secondary outcomes include:To pilot the recruitment and randomisation processes and assess their acceptability to clinicians and patients within the emergency setting;To assess the safety profile of emergency laparoscopic surgery;To explore the potential optimal endpoints, either clinical or patient-reported, that could be used as a primary endpoint in a definitive phase III trial;To explore the practical application and success of blinding in the emergency setting;To test the feasibility and refine the strategy for collecting patient-reported quality-of-life data and resource-use data to inform a future economic evaluation.

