## Trial interventions

### Surgery

For the purposes of this pragmatic trial, surgery, either open or laparoscopic, will be undertaken in accordance with local standard practice. Laparoscopic surgery includes the use of multiport and single-port incisions to establish pneumoperitoneum to enable surgical resection. Conversion to an open operation is defined as the use of a midline laparotomy wound for any part of the colorectal dissection. The use of a limited laparotomy wound to facilitate specimen extraction is permissible.

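### Putting conversion and safety rates on an intention-to-treat basis dilutes the conversion rate and mixes exposures in the laparoscopic safety profile

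*Protocol article*

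**What the plan says.** The protocol article's section on sample size and statistical analysis groups safety by arm: "The safety profile of each treatment arm will be summarised through descriptive statistics". It then lists the rates: "Mortality rates, intraoperative and postoperative complication rates, conversion rates and patient-safety indicator rates will be reported with 95% CIs". The next sentence sets the population for everything: "All analyses will be conducted on an intention-to-treat basis". It makes no exception for safety or conversion.

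The objectives are worded in terms of the operation. Under Secondary outcomes the aim is: "To assess the safety profile of emergency laparoscopic surgery". Under Safety: "To assess the safety profile of acute laparoscopic surgery, the following outcomes will be assessed: conversion rates from laparoscopic surgery to open surgery". The Surgery section defines the event: "Conversion to an open operation is defined as the use of a midline laparotomy wound for any part of the colorectal dissection".

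The article also allows for allocation and operation to differ. The recruitment logs record "the proportion of patients not receiving their randomised allocation and the reasons for this", and the Qualitative substudy lists "refusal of treatment allocation and burden of participation" among its interview topics. Non-receipt of allocation appears as a recruitment measure and is not carried into the safety analysis.

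**The concern.** The stated analysis set and the stated objective are different quantities whenever a patient does not have the allocated operation.

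- **Conversion.** Only an operation begun laparoscopically can be converted. On an intention-to-treat basis, a patient allocated to laparoscopy but opened from the start stays in the denominator without being able to contribute an event. The result is no longer a rate of conversion from laparoscopic surgery.
- **Complications, patient-safety indicators and mortality.** That same patient's events count as laparoscopic. The events of a patient allocated to open surgery but operated on laparoscopically count as open and drop out of the laparoscopic profile.

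The usual reason for accepting this is that it protects a randomised comparison, but the article says the arms will not be formally compared. The rates are descriptive, and the article presents them as showing the safety profile of the laparoscopic arm and as input to a phase III design. A conversion rate that is too low would mislead that design.

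**Working it through.** **Inputs.** At least 66 patients randomised 1:1 gives 66/2 = 33 allocated to laparoscopy. The stated precision is a 95% interval of at most ±17 points for the laparoscopic arm. The Background says about half of emergency abdominal operations started laparoscopically are completed that way; this is used only as an illustrative 50% conversion rate. The number never started laparoscopically, *m*, is not given and is varied as an assumption.

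**The plan's own figure.** The Wald half-width at its widest (p = 0.5) is 1.96 × √(0.25/n). With n = 33 it is 0.171, or 17.1 points, which agrees with the stated ±17 after rounding. The stated precision therefore corresponds to a denominator of all 33 allocated patients.

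**Conversion rate.** Let *k* be the conversions among the 33 − *m* operations started laparoscopically. The rate of interest is k/(33 − m). With every allocated patient in the denominator it becomes k/33, which is the rate among starts multiplied by (33 − m)/33.

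| m never started | Among starts | Over all 33 | Shortfall (points) |
|---|---|---|---|
| 0 | k/33 | k/33 | 0 |
| 3 | 15/30 = 50.0% | 15/33 = 45.5% | 4.5 |
| 5 | 14/28 = 50.0% | 14/33 = 42.4% | 7.6 |
| 7 | 13/26 = 50.0% | 13/33 = 39.4% | 10.6 |

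At a lower conversion rate the shortfall is smaller. With m = 5, 6/28 = 21.4% among starts becomes 6/33 = 18.2%, a shortfall of 3.2 points.

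**Complication rate.** If the true rates are p_L for operations started laparoscopically and p_O for operations opened from the start, the laparoscopic arm shows [(33 − m) × p_L + m × p_O]/33. This differs from p_L by (m/33) × (p_O − p_L). To show scale only, take the two ends of the 33% to 71% morbidity range in the Background. The document does not tie either end to an approach.

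- p_L = 33%, p_O = 71%, m = 5: (28 × 0.33 + 5 × 0.71)/33 = 12.79/33 = 38.8%, which is 5.8 points too high.
- The two rates exchanged, m = 5: (28 × 0.71 + 5 × 0.33)/33 = 21.53/33 = 65.2%, which is 5.8 points too low.

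The sign depends on rates that nobody has yet.

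**Precision on a started denominator.** The same half-width formula gives 17.9 points at 30 starts, 18.5 at 28 and 19.2 at 26.

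**The case against.** Five points can fairly be made on the other side.

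1. *Denominators and supplementary sets belong in the analysis plan, which is not shown.* This would hold if the article were silent. It is not: it names the conversion and safety rates and then applies one basis to all analyses. Intention-to-treat need not bar an extra table, nor must it force patients who cannot have an event into that event's denominator. But someone following the text as written would use the allocated arm.

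2. *Intention-to-treat by arm is a proper summary in a pragmatic trial that leads to a phase III comparison.* This stands in full. Grouping by the operation started selects on a decision taken after randomisation. If patients opened from the start are sicker, moving them out flatters laparoscopy. It is a reason to add a table, not to replace the arm summaries.

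3. *Few patients may fail to start.* Surgeon and anaesthetist must both judge the patient suitable for either approach, randomisation follows their assessment, and surgeons must meet experience thresholds. The document gives no non-receipt rate, so this stands, and the size above is conditional.

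4. *The shift lies inside the planned ±17 points.* True for the conversion cases shown. But a confidence interval describes sampling error and does not correct for a denominator that answers a different question.

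5. *The non-receipt log lets a reader recover the started denominator.* Only if it is reported by arm. It also does not change the rate the plan says it will report.

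A reader might also infer that the conversion rate could be overstated, because the definition under Surgery mentions only a midline wound. Primary open operations would then count as conversions, giving 18/33 = 54.5% with 3 never started or 20/33 = 60.6% with 7. The documents do not support this. The outcome under Safety is conversion from laparoscopic to open surgery, and read together the two sections do not make a primary open operation a conversion.

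**Conclusion.** The point holds as a mismatch between a stated analysis basis and a stated objective. Applied as written, the rule understates the conversion rate by the share of the laparoscopic arm never started. With 33 allocated and an assumed 50% conversion among starts, that is about 5 points at 3 non-starts and about 11 at 7. It is zero if every allocated patient is started laparoscopically. The 50% comes from emergency abdominal operations in general, not from the selected colorectal resections in this trial.

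For complications, patient-safety indicators and mortality, the arm summaries mix exposures, and the direction cannot be fixed beforehand. A reader might infer that intention-to-treat hides harm from laparoscopy. The documents give no approach-specific rates to support that, and the illustration can be made to run either way. Nor does the point mean that intention-to-treat should be dropped.

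The primary outcome, recruitment, is untouched. The wording should be changed because the descriptive safety results are meant to inform the next trial and the correction is cheap.

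**What to change.** In the section on sample size and statistical analysis:

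- Keep the intention-to-treat summaries by arm.
- State that the conversion rate is calculated among operations started laparoscopically, and that patients allocated to laparoscopy but not started are reported separately with reasons.
- Add a supplementary descriptive table of complications, patient-safety indicators and 30-day mortality by the approach with which surgery was started. Converted operations stay in the laparoscopic group.
- State that the as-started groups are not randomised and are not to be read as a comparison.

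The cost is a short addition to the text and a few descriptive tables. The operative details and the log of non-receipt are already to be collected. Intervals on the started denominator are slightly wider than the stated ±17 points: at worst about 18 to 19 points at 30 down to 26 starts.
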